***Exclusion criteria***

- Patients with hemodynamic instability after HT, including cardiogenic shock or severe coagulopathy.
- Patients with acute cellular rejection before intracoronary physiological assessment.
- Patients with bronchial asthma or bronchopathy with a positive bronchodilation test, which contraindicates the use of adenosine.
- Patients with epicardial coronary lesions with a resting physiological index ≤0.89 or ≤0.80 at hyperemia.
- Patients unlikely to cooperate or with inability or unwillingness to give informed consent.

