**- Secondary outcomes:**

-IMR variation between first three months after HT and one year: Comparison between the values of index of microvascular resistance (IMR) measured by bolus thermodilution technique between the first and 3rd month after HT and one year in the invasive physiological study. IMR may be expressed as mmHg·s.

-Acute cellular rejection: A ≥2R degree according to the 2010 ISHLT system. Two or more focal infiltration points associated with myocyte injury in EMB. Diffuse infiltration with multi-focal myocyte injury with/without oedema, hemorrhage or vasculitis.Time frame: One year.

-Cardiac allograft vasculopathy: Accelerated fibroproliferative process characterized by diffuse, concentric and longitudinal thickening of the intima of the vascular tree of the graft, affecting everything from the major epicardial arteries to the coronary microvasculature.Time frame: 5 years.

-Cardiovascular mortality:Caused by cardiovascular disease or unknown death. Time frame: 5 years.

-Heart failure: Diastolic or systolic heart failure after heart transplant. Time Frame: Five years.

-Inmunosupressive therapy: Changes in any of the inmunosuppresive agents pre-established in each center heart transplant protocol. Time Frame: Five years

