### 3.10.2. Retention

Clinical conditions, laboratory findings and clinical events will be assessed at one month and one year. A number will be assigned to each patient; their identity will not be disclosed in any case. All shared information will be anonymized. The principal investigator at each center will be responsible for keeping the data anonymized.

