**STUDY DESIGN**

**ENDPOINTS**

*The main objective* of the study is to evaluate IMR values and number of EMB performed in the first year after HT.

S*econdary endpoints* are:

- Analyze the relationship between ACR and IMR.
- Analyze the relationship between CV mortality and IMR.
- Analyze the relationship between CAV and IMR.
- Analyze the relationship between the variation IMR value in the first two months and one year, and cardiovascular events.
- Analyze the relationship between the combined endpoint of ACR, heart failure, re-transplantation, CV mortality and IMR.
- Assessment of immunosuppressive therapy after IMR results.

All endpoints will be evaluated at 1 year, and annually thereafter for up to 5 years.

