***Procedure***

**Invasive physiological evaluation of the coronary microcirculation**

Patients included will undergo a coronary angiography between the first and third month after HT.  This coronary angiography is part of the follow-up protocol in most of the centers. Assessment of IMR, coronary flow reserve (CFR) and fractional flow reserve (FFR) will be performed using the standard technique (9-10,14).

The left anterior descending coronary artery will be evaluated in all patients. Circumflex or right coronary artery could be additionally evaluated at operator’s discretion. An intracoronary pressure and temperature sensor-tipped guidewire (Pressure Wire TM X guide- wire 0.014’, Abbott, IL, USA) will be used to perform the measurements. The tip pressure sensor will be advanced into the mid-to-distal portion of the evaluated vessel. Baseline aortic pressure (Pa) and distal intracoronary pressure (Pd) will be obtained to calculate the resting index Pd/Pa. To measure the mean transit time (Tmn) under basal conditions, intracoronary administration of 3 mL of room-temperature saline will be manually injected three times in succession (3 mL/s). Then maximal hyperemia will be induced using adenosine iv (140 to 180 mg/kg/min) and three additional intracoronary room temperature saline boluses of 3 ml will be administered to determine the mean transit time at hyperemia (Tmnh). Finally, fractional flow reserve (FFR), coronary flow reserve (CFR) and IMR will be calculated using the software Coroventis Coroflow (*Coroventis Abbott, Uppsala, Sweden)*.

- FFR is defined as the ratio of maximal coronary blood flow in a diseased artery to maximal coronary blood flow in the same artery without stenosis. FFR is a surrogate marker of inducible myocardial ischemia caused by epicardial coronary stenosis.

- CFR is the ratio of hyperemic to baseline flow and is a marker of the integrity of both epicardial and microvascular coronary circulation. Therefore, CFR represents the microvascular status when there is no significant epicardial disease.

- IMR is the minimum achievable coronary microcirculatory resistance and a more specific marker of the coronary microcirculation. It is calculated as the ratio of distal coronary pressure to coronary flow at hyperemia and presented in units (mmHg.s).

The physiological study assessing IMR, CFR and FFR will be repeated again one year after HT.

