***Definition of principal variables***

- **Pa:** basal proximal (aortic) pressure.
- **Pah:** aortic pressure at maximal hyperemia.
- **Pd:** basal distal pressure.
- **Pdh:** distal pressure at maximal hyperemia.
- **Tmnr:** Mean transit time of the saline injected at rest.
- **Tmnh:** Mean transit time of the saline injected at maximal hyperemia.
- **RFR:** Resting index calculated on the basis of the lowest Pd/Pa value throughout the cardiac cycle. A value ≤0.89 is associated with functionally significant coronary stenosis.
- **FFR:** Hyperemic index calculated by Pdh/Pah quotient. FFR ≤0.80 is associated with functionally significant coronary stenosis.
- **CFR (coronary flow reserve):** This parameter explores the maximal vasodilation capacity of the entire coronary bed (epicardial and microvascular), and hence the increase in coronary flow compared with the resting value.

The fundamental principle is the inversely proportional relationship between the coronary flow and transit time (TT) of a bolus of intracoronary saline, estimated on the basis of the change in temperature. CFR is considered to be low when is <2; normal >2.5.

CFR= 1/(Tmnh/Tmnr)

- **IMR (index of microcirculatory resistance):** This index reflects microvascular function regardless of epicardial circulation. It is obtained in a state of maximal hyperemia. A value ≥25 is considered pathological; normal <20. In our study, an IMR ≥15 will be considered high (8).

IMR= Pdh x Tmnh.

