***Definition of events***

- **Acute cellular rejection (ACR**): A ≥2R degree according to the 2010 ISHLT system. Two or more focal infiltration points associated with myocyte injury in EMB. Diffuse infiltration with multi-focal myocyte injury with/without oedema, hemorrhage or vasculitis (2).
- **Cardiovascular mortality:** Caused by cardiovascular disease or unknown death.
- **Cardiac allograft vasculopathy:** Accelerated fibroproliferative process characterized by diffuse, concentric and longitudinal thickening of the intima of the vascular tree of the graft, affecting everything from the major epicardial arteries to the coronary microvasculature (2).
- **Combined endpoint:** ACR, heart failure, re-transplantation and cardiovascular mortality.
- **Cardiac catheterization complications:** any complication (major or minor) related to the performance of EMB, coronary angiography and functional study.

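### Heart failure that begins before the early IMR study qualifies for the composite endpoint that is related to IMR

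*Protocol*

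**What the plan says.** **Outcome.** Protocol section 3.4 (secondary outcomes) defines heart failure as "Diastolic or systolic heart failure after heart transplant. Time Frame: Five years". Under Definition of events, the combined endpoint is "ACR, heart failure, re-transplantation and cardiovascular mortality". Neither entry says when heart failure must begin relative to the IMR study.

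**Exposure.** The Procedure section states: "Patients included will undergo a coronary angiography between the first and third month after HT". IMR is measured at that examination and again at one year. A value of 15 or more counts as high.

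**Link between the two.** One of the secondary endpoints is "Analyze the relationship between the combined endpoint of ACR, heart failure, re-transplantation, CV mortality and IMR". Section 2.2 lists the same relationship, with all-cause mortality added to the composite. The statistical sections (3.12.1 and the later Statistical analysis) compare events between groups by Kaplan-Meier curves and use Cox regression for adjustment. They give no time origin.

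**Eligibility.** The exclusion criteria include "Patients with acute cellular rejection before intracoronary physiological assessment". The nearest criterion that touches heart failure is "Patients with hemodynamic instability after HT, including cardiogenic shock or severe coagulopathy".

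**Event collection.** Section 3.10.2 and the Data and follow-up section state: "Clinical conditions, laboratory findings and clinical events will be assessed at one month and one year". The Study variables table marks follow-up events only at 12 months and annually, not at the month 1-2 visit where the functional coronary test is done.

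**The concern.** A prognostic comparison needs the exposure to come before the outcome. The protocol secures this for rejection, by excluding patients who had it before the physiological study. It has no matching rule for heart failure, another component of the same composite. A patient with non-shock heart failure a few weeks after transplant can be enrolled and have IMR measured later, and that episode then meets the composite definition.

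Early graft dysfunction may itself go with a raised IMR. If it does, part of any composite-by-IMR association would describe the state of the graft when IMR was measured and not what followed. The error would make IMR look more prognostic than it is. That bears on the stated aim of learning whether management can safely be modified on the IMR value. Within a first-event analysis of the composite, an early heart failure event would also take the place of any later component event in the same patient.

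**Working it through.** The protocol states no rate, effect size or power for heart failure, so there is no figure of its own to reproduce. The check has two parts.

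**1. Does any part of the protocol remove pre-IMR heart failure?**

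- *Outcome definitions (3.4, Definition of events):* no condition on onset.
- *Exclusions:* earlier rejection is removed and so is hemodynamic instability, but milder or resolved early heart failure is not.
- *Analysis text:* no landmark and no time zero at the IMR study.
- *Event collection:* section 3.10.2 assesses events at one month, at or before the opening of the IMR window. The Study variables table records them at 12 months and annually, and a 12-month form can look back to transplant. The two differ, and neither separates heart failure before IMR from heart failure after it.

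So nothing removes it. The period at issue is 1/12 to 3/12 (8.3% to 25%) of the first year, or 1/60 to 3/60 (1.7% to 5%) of five years.

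**2. How large could the distortion of the composite be?**

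All inputs here are assumptions; none is in the protocol.

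- The low-IMR and high-IMR groups are of equal size.
- There is no true effect after IMR: risk of post-IMR rejection is 16% and of post-IMR heart failure *h* = 10%, the same in both groups and independent.
- Overall pre-IMR heart failure is *p*, and its odds ratio with high IMR is OR.

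Formulas:

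- Pre-IMR risks *a* (low IMR) and *b* (high IMR) solve (*a* + *b*)/2 = *p* and [*b*/(1 − *b*)] / [*a*/(1 − *a*)] = OR.
- Post-IMR composite risk *q* = 1 − (1 − 0.16)(1 − *h*). With *h* = 10%, *q* = 1 − 0.84 × 0.90 = 0.244.
- Counted composite risk = *a* + (1 − *a*)*q* and *b* + (1 − *b*)*q*. The apparent risk ratio is the second divided by the first.

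Example with *p* = 10% and OR 2: *a* = 0.0697 and *b* = 0.1303. Low IMR: 0.0697 + 0.9303 × 0.244 = 0.297. High IMR: 0.1303 + 0.8697 × 0.244 = 0.342. Ratio 1.15.

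| *p* | OR | *h* | *a* | *b* | Composite, low IMR | Composite, high IMR | Risk ratio |
|---|---|---|---|---|---|---|---|
| 10% | 1 | 10% | 0.100 | 0.100 | 0.320 | 0.320 | 1.00 |
| 5% | 1.5 | 10% | 0.041 | 0.059 | 0.275 | 0.289 | 1.05 |
| 10% | 2 | 10% | 0.070 | 0.130 | 0.297 | 0.342 | 1.15 |
| 15% | 3 | 10% | 0.084 | 0.216 | 0.308 | 0.407 | 1.32 |
| 2% | 2 | 20% | 0.013 | 0.027 | 0.337 | 0.346 | 1.03 |

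The last row uses *q* = 1 − 0.84 × 0.80 = 0.328. The true ratio is 1 in every row, so any excess over 1 comes only from counting pre-IMR heart failure. Re-transplantation and cardiovascular death are left out of *q*; adding them at equal rates would pull every ratio closer to 1.

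**The case against.** Several points on the other side carry weight.

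- **The time origin is not fixed.** A reader might infer that the protocol commits to analysing pre-IMR heart failure as an outcome. It does not go that far. The phrase about heart failure after transplant can be read as naming heart failure in the graft, as distinct from the disease that led to transplant. A statistical analysis plan, not shown here, could set a landmark. This stands, so the claim is limited to what qualifies under the definition. A landmark would still have to narrow the protocol's outcome, and the date of onset would have to be collected for it to work.
- **The Study variables table suggests events are collected after the IMR visit.** In part it does, but the one-month assessment in section 3.10.2 differs, and a 12-month form does not by itself exclude earlier onset.
- **Baseline information partly exists.** Echocardiogram and medication are recorded at screening and at 1-2 months, clinical conditions are assessed at one month, and Cox adjustment is planned. This helps, but no heart failure field is named, and adjustment does not stop a pre-exposure episode from counting as the event.
- **Heart failure alone is not related to IMR in any listed objective.** A reader might quote the apparent risk ratio for heart failure by itself (1.13 to 1.68 over *p* of 5-15% and OR 1.5-3). No listed objective uses it, so only the composite figures are relevant.
- **Masking is limited.** A reader might infer that later rejection or cardiovascular death is lost. Both are also related to IMR separately, so masking can occur only within a first-event analysis of the composite.
- **The larger ratios depend on the inputs.** This stands. An odds ratio range starting at 1.5 builds in bias, and the instability exclusion removes the worst early cases, which makes a high residual rate harder to assume. With no link the ratio is 1.00, and the milder inputs give 1.03.

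**Conclusion.** The point holds in a limited form. As defined, heart failure that began before the month 1-3 IMR study can enter the composite related to IMR. The protocol guards against this for rejection but not for heart failure, and nothing else in it closes the gap.

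The direction of bias is towards a falsely prognostic IMR, provided that early heart failure goes with higher IMR. The documents neither show nor rule out that link. The size is unknown. Under the stated assumptions and no true effect, the composite risk ratio lies between 1.0 and about 1.3, and is about 1.15 at 10% pre-IMR heart failure with an odds ratio of 2.

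The reach is one component of one secondary composite. The primary endpoint (IMR values and number of biopsies in the first year) and the separate rejection and cardiovascular mortality analyses are not affected.

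**What to change.** 1. In section 3.4 and under Definition of events, count heart failure as an event, alone and within the composite, only when its onset is after the early IMR study.
2. In the statistical section, start time-to-event follow-up for the IMR comparisons at the date of that study.
3. Record heart failure between transplant and that study as a baseline yes/no variable and include it as a covariate.
4. Bring section 3.10.2, Data and follow-up, and the Study variables table into agreement on when events are collected, and collect the date of heart failure onset.

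The cost is wording, one added data field and slightly fewer heart failure events. Eligibility and patient care do not change.

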## 5.3. Roles and responsibilities

### 5.3.1. Protocol contributors

**Index of microvascular resistance (IMR)-guided management of heart transplantation**

**IMR-Heart Transplant Study**

**PROTOCOL**

**SUMMARY**

| **Study title** | INDEX OF MICROVASCULAR RESISTANCE-GUIDED MANAGEMENT OF HEART TRANSPLANTATION |
| --- | --- |
| **Short Running Title** | IMR-HEART TRANSPLANT STUDY |
| **Investigators** | [name]  [name]  [name]  [name] |
| **Study aim** | Follow-up assessment of heart transplant patients based on IMR |
| **Hypothesis** | The index of microvascular resistance will serve to reduce the number of endomyocardial biopsies in transplant patients. |
| **Study design** | Multi-center, prospective, observational |
| **Inclusion criteria** | Heart transplant patients >18 years. |
| **Exclusion criteria** | Patients presenting with hemodynamic instability after HT, including cardiogenic shock or severe coagulopathy. Patients with acute cellular rejection before intracoronary physiological assessment. Patients with bronchial asthma or bronchopathy with a positive bronchodilation test, which contraindicates the use of adenosine. Patients with epicardial coronary lesions with a resting physiological index ≤0.89 or ≤0.80 at hyperemia. Patients unlikely to cooperate in the study or with inability or unwillingness to give informed consent. |
| **Primary endpoint** | Number of biopsies performed in the first year.  IMR in transplant patients, in the first three months and one year. |
| **Secondary endpoints** | Cardiovascular mortality and IMR.  Cardiac allograft vasculopathy and IMR.  Acute cellular rejection and IMR.  IMR variation, in the first two months and at one year.  Combined endpoint of ACR, heart failure, re-transplantation, cardiovascular mortality and IMR.  Immunosuppressive therapy and IMR. |
| **Data analysis** | Observational, analytical |
| **Follow-up** | 1 year and annually for five years |

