**STUDY VARIABLES**

| **Event** | **Screening** | **1-2 month(s)**  **post-transplantation** | **12 months**  **post-transplantation** | **Annual**  **for 5 years** |
| --- | --- | --- | --- | --- |
| **Criteria** **for**  **inclusion/exclusion** | X |  |  |  |
| **Informed**  **consent** | X |  |  |  |
| **Laboratory test** | X | X |  |  |
| **Echocardiogram** | X | X | X |  |
| **Medication** | X | X | X |  |
| **Functional invasive coronary test** |  | X | X |  |
| **Events during**  **follow-up** |  |  | X | X |

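### The five-year immunosuppression outcome has no scheduled medication collection after month 12, and the protocol's follow-up statements disagree with one another

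*Protocol*

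**What the plan says.** Section 3.4 sets the time frame of each secondary outcome. For immunosuppressive therapy it reads "Changes in any of the inmunosuppresive agents pre-established in each center heart transplant protocol. Time Frame: Five years". Cardiac allograft vasculopathy and heart failure also have five years, as does cardiovascular mortality ("Caused by cardiovascular disease or unknown death. Time frame: 5 years"). Acute cellular rejection (ACR) is shorter ("hemorrhage or vasculitis.Time frame: One year"), and IMR variation ends at the one-year study.

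The embedded protocol under section 5.3.1 lists "Assessment of immunosuppressive therapy after IMR results" among its secondary endpoints and then states: "All endpoints will be evaluated at 1 year, and annually thereafter for up to 5 years". Its summary table gives follow-up as "1 year and annually for five years".

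The Study variables table has four columns: screening, 1–2 months, 12 months, and annual to five years. The medication row reads "Medication | X | X | X", with the fourth cell empty. The row for events is marked at 12 months and in the annual column.

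Section 3.10.2 and the Data and follow-up text contain the same sentence: "Clinical conditions, laboratory findings and clinical events will be assessed at one month and one year". Neither mentions a later time point.

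**The concern.** A five-year outcome defined by drug changes needs drug data for five years. The schedule is the only place that times the collection of medication, and it stops at month 12. A site that follows it correctly will hold no planned record of changes in years 2 to 5.

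The late period matters on the protocol's own reasoning. The introduction to the embedded protocol names graft vasculopathy as the leading cause of death after the first year, describes one drug class as used mainly for that condition, and suggests that a high IMR might prompt its earlier use. The physiology study is repeated at one year. Any drug change prompted by that second result would come after the last scheduled medication entry, yet the stated endpoint is therapy after the IMR results.

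The conflicting follow-up statements add a second risk. Sites have two descriptions of how long patients are followed, and the protocol does not say which one governs.

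**Working it through.** No formula applies and the protocol gives no figure to reproduce. The check sets the statements side by side.

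| Item | Outcome time frame | Study variables schedule | Section 3.10.2 and Data and follow-up |
|---|---|---|---|
| Immunosuppression changes | 5 years (3.4; Endpoints) | Screening, 1–2 months, 12 months | Medication not mentioned |
| Vasculopathy, cardiovascular mortality, heart failure | 5 years (3.4; Endpoints) | Events at 12 months and annually | 1 month and 1 year |
| ACR | 1 year (3.4); up to 5 years (Endpoints) | Events at 12 months and annually | 1 month and 1 year |
| Laboratory tests | No listed outcome | Screening, 1–2 months | 1 month and 1 year |

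1. **Medication.** There are three scheduled collection points, and none after month 12. The uncovered part of the time frame is 5 − 1 = 4 years, or 4/5 = 80% of calendar time. The empty cell looks deliberate and not like a broken table, because the events row carries a mark in the same column. No other schedule fills the gap: the timeline in section 3.5 is an unfilled template with every entry in its first column.

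2. **Which drug changes are lost.** The first physiology study is at one to three months (Procedure). Changes prompted by it would ordinarily fall before the 12-month medication entry, so they are covered. Changes after the 12-month entry, including those that follow the one-year IMR, are not. The 80% is a share of calendar time and not a share of IMR-prompted changes.

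3. **Duration of follow-up.** Three places run to five years: the Follow-up row of the summary table, the annual events row of the schedule, and the Endpoints sentence. Two places name only one month and one year: section 3.10.2 and Data and follow-up. This is a contradiction within the document.

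4. **Laboratory tests.** The follow-up sentence includes laboratory findings at one year. The schedule has no laboratory mark at 12 months.

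5. **ACR.** Section 3.4 gives one year. The Endpoints sentence covers every endpoint, and ACR is on that list, so there it runs to as much as five years. ACR is also part of the combined endpoint, so the choice decides whether rejection after year 1 counts there.

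**The case against.** The strongest reply is that the protocol does plan five-year follow-up. The summary table says so, the Endpoints text commits to evaluating every endpoint annually, and the schedule marks events each year. A site reading the whole document would be unlikely to stop at year 1. The changes of most interest, those made in response to the early IMR, fall within the period when medication is recorded. All of this stands, and it limits the point.

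Three stronger readings are tempting, and the documents do not support them.

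- A reader might infer that the five-year immunosuppression outcome cannot be produced at all. The Endpoints text commits to evaluating it, and drug histories might be recovered from clinical records. What is missing is a scheduled source for them.
- A reader might infer from section 3.10.2 that events in years 2 to 5 will all be missing. That would require sites to ignore the summary, the schedule and the Endpoints text.
- A reader might infer repeated significance testing of each endpoint every year at 0.05. The protocol says endpoints are evaluated, which need not mean tested. Its only stated analysis trigger is 100 patients completing one year, and Kaplan-Meier and Cox methods can use accumulated follow-up in one analysis.

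The absence of an events mark at 1–2 months is also harmless if the 12-month entry covers the preceding period.

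The reply does not supply the missing medication cell or reconcile the follow-up sentence. Nor can these be left to a statistical analysis plan: the visit schedule is protocol content, and an analysis plan cannot analyse data that sites were not told to collect.

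**Conclusion.** The point holds in a limited form. One stated secondary outcome, immunosuppressive therapy, has no planned data source for four of its five years. The follow-up sentence that appears in two places conflicts with the five-year follow-up stated in three others and with the 12-month laboratory cell. ACR has two time frames.

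The first-year biopsy count and the one-year IMR comparison are unaffected by the medication gap. The five-year event outcomes are covered provided sites follow the schedule. The laboratory mismatch is minor, because no listed outcome is a laboratory value.

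The conclusion assumes that the Study variables table is the operative schedule and that the REDCap forms, which are not shown, collect what it marks. If those forms already ask for medication annually, only the text needs correcting. The change should be made, because the defect is plain on the page and cheap to repair.

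**What to change.** - In the Study variables table, mark medication in the annual column. Alternatively, limit the immunosuppression outcome in section 3.4 to the 12 months collected and exempt it from the Endpoints sentence on annual evaluation.
- In section 3.10.2 and Data and follow-up, extend the follow-up sentence to include annual follow-up to five years.
- Align the laboratory row with that sentence, by marking 12 months or by removing laboratory findings at one year from the text.
- Give ACR one time frame in section 3.4 and under Endpoints, and say whether the same limit applies to ACR within the combined endpoint.

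The cost is an amendment to one table and a few sentences, plus a short medication form at annual contacts already planned. With the target of 100 patients and four annual contacts after month 12 (years 2 to 5), that is at most 100 × 4 = 400 short forms, and fewer with deaths or losses. The trial summary dates enrolment from March 2024, so the longer the amendment waits, the more late drug data would have to be recovered retrospectively. Choosing the shorter time frame avoids the forms but gives up information on later drug changes, including those after the one-year IMR.
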